### **Inclusion**

This trial relates to care practice. In order to meet the main objective, it requires homogeneity of intubation fixation practices within a given department during each of both inclusion periods, regardless of the status of the patient in the study (included or not).

Thus, in each ICU participating in the project, whatever the inclusion arm considered (A or B), all patients requiring invasive mechanical ventilation (MV) from their admission to the intensive care unit (if the respiratory assistance was set up before admission to the intensive care unit) or from the moment the respiratory assistance was set up (if it was set up in the intensive care unit), will benefit from the fixation method according to the inclusion arm (A or B) described above, whether they are included in the study or not. D0 is defined as the first day of the study fixation system of the ETT (cord + sheath or elastic adhesive bands).

Information and consent to participate in the study will be sought from patients requiring MV (or their relatives), who meet all the inclusion criteria and have no non-inclusion criteria (see chapter 3.3).

In the absence of the physical presence of the trusted support person or a relative, an emergency procedure will be available to include the patient. In all cases, the relative and then the patient will be informed as soon as possible by the investigator who will deliver the information note and the collection of their oral consent will be carried out secondarily by the investigator.

After having ensured the consent of the patient or his relatives or having followed the emergency inclusion procedure, the investigator can then include the patient before the D1 photograph. Moreover, if the information was initially given to the relatives, the consent will also be sought from the patient as soon as his level of vigilance allows it.

One of the criteria for non-inclusion of the patient is the presence of pre-existing facial lesions on arrival in the ICU in the path of the endotracheal tube fixation.

When the patient is admitted to the ICU already intubated, the tube is already fixed and this fixation is generally changed in order to put in place the fixation system used in the department. Within the framework of the protocol, we will ask that it be systematically changed to install the fixation system under study. The non-inclusion criterion can therefore be assessed at this point.

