## Follow-up

During the two recruitment periods, a logbook will be given to the paramedical staff and will include the follow-up of each change of fixation made during their stay in the ICU.

The notebook will also record the presence of vasopressors, prone positioning, extubation or re-intubation, or the presence of sedation, which are risk factors for injury in resuscitation patients.

The nurse in charge of the patient will have to change the fixation system at least once a day and if necessary during the day in case of soiling or examinations.

Duoderm-type dressings used to prevent pressure sores under the endotracheal tube will not be accepted, since this is the subject of the study. However, it can be applied as a curative measure if a lesion appears.

A verification of the correct positioning of the endotracheal tube thanks to the graduated marker will be systematically carried out once a day. If a repositioning is necessary the nurse will note the number of centimeters (either at the bottom or at the top). The mobilization of the tube (change of side) will be performed according to the usual practices of the service.

The number of mobilizations, interventions (e.g., retying the knot) on the fixation system and the number of fixation system changes will be recorded daily.

The presence or absence of lesions will be assessed daily by the nurse in charge of the patient. She will also assess the type of lesion: cutaneous or mucous and depending on the type will use the appropriate scale to assess the grade: NPUAP scale (cutaneous) or / and the ROMPIS scale (mucous).

Two photos (one with the lower lip visible and one with the upper lip visible) will be taken every day by the nurses from the day of the first fixation change = D0 until D10. In no case will the whole face of the patient be taken. The patient will not be identifiable. The photos will be taken without the fixation visible to allow the blind to be kept for the committee that will evaluate the photos. The photos will be identified only by the patient's number and the date.

Each expert will have to record the presence or not of a peri-oral lesion between D0 and D10 of maintenance of respiratory assistance via an endotracheal tube. .

For the primary endpoint, we selected a daily photo assessment until D10. The choice of this time frame was based on:

- the time of appearance of peri-oral lesions (more than 50% of them appear during the first 5 days) (7)

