## FIXATUB protocol

- the average duration of ventilation for patients who require invasive respiratory assistance for more than 48 hours
- risk factors for pressure ulcers which are essentially present at the beginning of the management of patients in shock (oedema, sedation, decrease in tissue perfusion, undernutrition, vasopressor treatments)

The follow-up by the nurse's notebook will stop at the final extubation or at the discharge from the ICU if the patient is discharged intubated from the ICU before D28 or at most D28.

|                              |
|------------------------------|
| SCHEDULE OF THE STUDY |
|------------------------------|

| Actions                                                                                             | D0 | D1 | D2 | D3 | D4 | D5 | D6 | D7 | D8 | D9 | D10 | D22 to D27 | D28 |
|-----------------------------------------------------------------------------------------------------|----|----|----|----|----|----|----|----|----|----|-----|------------|-----|
| Inclusion / non-inclusion criteria                                                                  | X  |    |    |    |    |    |    |    |    |    |     |            |     |
| Participation agreement                                                                             | X  |    |    |    |    |    |    |    |    |    |     |            |     |
| Biological assessment for SOFA                                                                      | X  |    |    |    |    |    |    |    |    |    |     |            |     |
| Assessment of peri-oral lesions:                                                             |    |    |    |    |    |    |    |    |    |    |     |            |     |
| ▮ Paramedical examination (peri-oral lesion survey)                                                 | X  | X  | X  | X  | X  | X  | X  | X  | X  | X  | X   | X          | X   |
| ▮ Photographs (during the change of the fixation system)                                            | X  | X  | X  | X  | X  | X  | X  | X  | X  | X  | X   |            |     |
| Collection of endotracheal tube mobilizations                                                       | X  | X  | X  | X  | X  | X  | X  | X  | X  | X  | X   | X          | X   |
| Collection of the repositioning of the endotracheal tube                                            | X  | X  | X  | X  | X  | X  | X  | X  | X  | X  | X   | X          | X   |

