### **Analysis of the assessment criteria**

To account for the study design, all criteria (primary and secondary) will be compared using hierarchical generalized linear models. The type of fixation, the period and the center (=cluster) will be taken into account in the model as fixed effects; the center\*period interaction will be taken into account as a random effect (14).

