#### Main criterion

The percentage of patients with at least one peri-oral lesion will be estimated with a 95% confidence interval for both types of fixation. A logistic regression model taking into account the duration of the patient's endotracheal tube retention and the study design will be applied.

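### The primary model adjusts for no patient baseline characteristic, although SOFA is collected at D0, so systematic selection within a centre between its two fixation periods would bias the fixation effect

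*Protocol*

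**What the plan says.** Protocol section 6.2.1 (Analysis of the assessment criteria) sets one model structure for all criteria: "The type of fixation, the period and the center (=cluster) will be taken into account in the model as fixed effects". The centre-by-period "interaction will be taken into account as a random effect". Under Main criterion it adds: "A logistic regression model taking into account the duration of the patient's endotracheal tube retention and the study design will be applied". Tube-retention time is the only patient-level term named, and it is a post-baseline quantity. Baseline features are described by period and sequence, and no analysis is attached to them.

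The schedule table in section 4.3 has the row "Biological assessment for SOFA", ticked at D0 only. SOFA is mentioned in no analysis. Section 4.3 (Follow-up) says: "The notebook will also record the presence of vasopressors, prone positioning, extubation or re-intubation, or the presence of sedation", and calls these items risk factors for injury.

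On recruitment, section 6.2.8 randomises the order of the two systems by centre, before the study starts. Section 4.1 describes an open study. In section 4.3 (Inclusion), every ventilated patient in the unit receives the allocated system, and "the investigator can then include the patient before the D1 photograph".

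**The concern.** In an individually randomised trial, allocation after enrolment protects the comparison of patients. Here allocation comes first, it is known to the staff, and the decision to include follows placement of the fixation. Several entry conditions need judgement: the expected duration of intubation, a high probability of early death, and pre-existing facial lesions, which may be assessed when the study fixation is installed (sections 3.2, 3.3 and 4.3). There is also some room to choose. Section 3.1 reports 927 patients in 20 months from 10 of the centres under nearly the same criteria, which is 927 / (20 × 10) = 4.6 per centre per month. The target of 24 per 12-month period is 2 per month.

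Suppose staff enrol a different severity mix under tape than under cord. The centre effect removes what is stable in a centre, and the period effect removes what all centres share over time. Neither removes a within-centre difference that follows the fixation system, because that difference lines up with the treatment term itself. Part of the reported fixation effect would then be case mix. The D0 measure that could remove the severity part is already collected.

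**Working it through.** **1. The plan's own figure.** Inputs from section 6.2.2: 35% against 20%, 90% power, alpha 5% (taken as two-sided), intra-class correlation 0.10, inter-class correlation 0.05, 16 centres, 24 patients per centre-period.

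- Individually randomised, pooled variance: n = [1.96·√(2·0.275·0.725) + 1.2816·√(0.35·0.65 + 0.20·0.80)]² / 0.15² = 185 per arm after rounding up.
- Design effect: 1 + (24 − 1)·0.10 − 24·0.05 = 2.1.
- Total: 2 · 185 · 2.1 = 777. With unpooled variance: 2 · 180.96 · 2.1 = 760.

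The stated 768 lies between the two. Power at 384 per arm is 89.8%. The sample size is sound and the present point does not change it.

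**2. Chance imbalance.** I simulated 16 centres × 2 periods × 24 patients with centre and centre-period random effects, no true effect, and a binary risk factor (50% prevalence, odds ratio 2). The analysis used within-centre period differences on 16 − 2 = 14 df, with 3,000 runs. With no systematic imbalance, the unadjusted analysis had a bias of −0.1 points and rejected 5.1% of the time. Chance differences in case mix are therefore already covered by the standard error.

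**3. Systematic selection on a continuous severity score.** Assumptions, none of them in the documents: no true effect, average risk 27.5% (midpoint of 35% and 20%), severity standard normal, tape patients 0.3 SD less severe, lesion odds ratio OR per SD.

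- Arm risks: the average of expit(b + ln(OR)·(x ± 0.15)) over x ~ N(0,1), with b set so that the average risk at zero shift is 27.5%.
- Standard error of the risk difference: √(2 · 0.275 · 0.725 · 2.1 / 384) = 0.0467.
- Rejection: two-sided t test, 14 df, non-centrality = difference / 0.0467.

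| OR per SD | Cord risk | Tape risk | Spurious difference | Share of 15 points | Type I error |
|---|---|---|---|---|---|
| 1.3 | 28.3% | 26.7% | 1.5 points | 10% | 6.1% |
| 1.5 | 28.7% | 26.3% | 2.3 points | 16% | 7.6% |
| 2.0 | 29.4% | 25.6% | 3.8 points | 25% | 11.8% |

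**4. Cross-check with a binary risk factor.** Same average risk, 50% prevalence, prevalence differing between arms by 10 or 20 points, normal approximation:

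- OR 2: 1.4 or 2.7 points, type I error 6.0% or 9.0%.
- OR 3: 2.1 or 4.2 points, type I error 7.4% or 14.7%.

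The simulation of step 2 with OR 2 gave unadjusted biases of −1.3 and −2.5 points, with rejection of 6.2% and 8.0%. After correction for the factor, with its slope supplied at 0.135, bias was within 0.2 points and rejection 4.5% to 4.9%. This shows only that the bias can be removed when the factor behind it is measured.

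**The case against.** The best defence is that a design-based model is a legitimate primary analysis, and that prognostic covariates are often left to a SAP, which is not at hand. The protocol names terms without excluding others. It also has safeguards: each centre is its own control over a full year per arm, all intubated patients receive the allocated system and are photographed on admission, a log records reasons for non-inclusion, emergency inclusion reduces dependence on relatives, and vasopressor use is required partly to make patients alike. Most of this stands, and it makes selection less likely and easier to see. It does not correct an estimate if selection occurs. Nor is covariate choice simply left open, since the protocol itself picks one patient-level covariate and it is a post-baseline one.

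Four stronger readings are tempting but not supported.

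- A reader might infer that any difference in severity between arms passes straight into the fixation effect. Stable centre differences, common time trends and chance centre-by-period shifts do not; only systematic selection biases the estimate.
- A reader might infer that all the named risk factors are ready-made baseline covariates. Vasopressor use is an entry criterion and so cannot differ at entry. Sedation and prone positioning belong to a follow-up notebook and have no row in the schedule.
- A reader might infer that the documents link SOFA to lesions. They do not; SOFA is simply the one severity measure clearly scheduled at D0.
- A reader might infer that no adjustment is planned at all. The unseen SAP may contain one, so the point concerns the model as the protocol states it.

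The calculations have limits too. They use centre differences and not the stated logistic mixed model, and they contain no retention-time term, which might absorb part of a severity difference.

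**Conclusion.** The point holds in a limited form. As written, the primary model has no patient baseline covariate, and the order of events (open allocation, then fixation, then inclusion) leaves a route for selection within centres that centre and period terms cannot close. Under the assumed 0.3 SD severity difference and lesion odds ratios of 1.3 to 2.0 per SD, the spurious effect is about 1.5 to 3.8 points, or 10% to 25% of the planned difference, with type I error of about 6% to 12%. That is modest, and it becomes material only if the imbalance and the association are both sizeable. Nothing in the documents shows that such selection occurs. The case for acting is that the remedy costs almost nothing and is credible only if it is fixed before the data are seen.

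**What to change.** In section 6.2.1, before database lock:

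- Add D0 SOFA (linear) as a pre-specified patient-level fixed covariate in the primary model, with simple baseline imputation of missing SOFA so that no patient is dropped.
- Add sedation and prone positioning only if the notebook holds a value fixed at D0. Later values must not be used.
- Keep the model without these covariates as a sensitivity analysis.
- Report a standardised risk difference beside the odds ratio, which becomes conditional on SOFA.

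The cost is a sentence or two and one extra parameter, set against about 384 · 0.35 + 384 · 0.20 = 211 expected events. No new data are needed for SOFA, and the sample size stays at 768. Simulated power with and without SOFA was within a point (88.0% and 88.7%, 700 runs, Monte Carlo error about 1 point). The adjustment handles measured severity only. Selection on features that SOFA does not capture would remain, so the screening log should also be used to compare included and non-included eligible patients by fixation system.

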#### Main criterion

The percentage of patients with at least one peri-oral lesion will be estimated with a 95% confidence interval for both types of fixation. A logistic regression model taking into account the duration of the patient's endotracheal tube retention and the study design will be applied.

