## **2. OBJECTIVES AND EVALUATION CRITERIA**

### **2.1. OBJECTIVE AND MAIN EVALUATION CRITERION**

#### **2.1.1. Main objective**

To demonstrate that the elastic adhesive tape fixation strategy decreases the risk for developing a peri-oral lesion before the 10th day of maintaining the orally inserted ETT.

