#### **2.1.2. Primary endpoint**

Appearance of at least one peri-oral lesion during the first ten days of maintaining the orally inserted endotracheal tube.

The peri-oral lesion will be validated on photographs by an independent review committee. The photos will be taken daily, taking the precaution that the fixation system is not visible (maintaining the blindness for the adjudication committee) from D0 to D10.

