### **2.2. SECONDARY OBJECTIVES AND EVALUATION CRITERIA**

#### **2.2.1. Secondary Objective(s)**

- Verify the effectiveness of the device in maintaining the endotracheal tube in terms of self-extubation from intubation until extubation or D28.
- Verify the effectiveness of the device in maintaining the endotracheal tube in terms of repositioning the tube from intubation until extubation or D28.
- Compare the time to the first peri-oral lesion from intubation to extubation or D28.
- Compare the intensity of peri-oral skin lesions assessed by nurses from intubation till extubation or D28.
- Compare the intensity of mucosal peri-oral lesions assessed by nurses from intubation till extubation or D28.

- Assessing the incidence of peri-oral lesions
- Evaluate the impact of the intervention on the maximum number of lesions per day.

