### 5.2.2. Adverse events / Expected incidents

- List of Incidents/Expected Events related to the investigational medical device/comparator

- *The medical device under study (elastic adhesive tape):*

The MD is used in its indication: fixation.

(There is no detailed AE in the technical data sheet except for one contraindication: subjects sensitized to synthetic products).

Expected Incidents / AE:

- Intolerance to synthetic products
- Skin lesions and mucosal lesions in the path of fixation. (*13% of patients according to reference 7*)
- Loss of adhesiveness of the tape.

- *The medical device comparator (cord + sheath):*

The comparator is used in its indication: fixation.  
There are no AE detailed in the technical data sheet.

Expected Incidents / AE:

- Skin and mucosal lesions in the path of fixation (*43% of patients in reference 7*)
- Shearing, potential cut due to cord.

- List of expected AEs related to investigative procedures:

- *Medical device implementation:*

- Unscheduled extubations: self-extubations and accidental extubations during care (*7 to 16% of patients depending on reference 17*)
- Tracheal complications including laryngeal dyspnea
- Ventilator-associated pneumonia.

- List of expected AEs related to other additional procedures:

- *Auxiliary Drugs/MDs:*

- *Anti-adhesive (elastic adhesive tape group) to remove residual glue.*
- *Duoderm ® or other dressings used in curative treatment in case of lesions.*
- *Cavilon ™ type skin protection film.*

As these treatments are prescribed within the scope of their indications, any AEs for them are described in the respective summary of product characteristics (SPC)s, which serve as a reference.

-

*To the procedures performed, methods/techniques used for the purpose of the research:*

NA

- List of AEs related to the studied disease (death due to the disease, relapse, ...):

The patients included will be patients hospitalized in the intensive care unit, most often with multiple pathologies, who are intubated and put on invasive mechanical ventilation.

The potential complications of intensive care management of the study patients are identical to those expected in the non-study population, including, but not limited to, nosocomial infections, complications of intubation procedures, anesthesia drugs, consequences of prolonged bed rest, occurrence of shock with a risk of multi-visceral failure, and death.

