#### Secondary criteria

The number of self-extubations, repositioning of the ETT will be estimated and compared using a Poisson regression model taking into account the study design. An offset of the logarithm of the intubation time will be included in the model.

The time to the first peri-oral lesion will be estimated using a random-effects survival model to account for the study design.

The time to onset will be calculated from the date of intubation to the date of first lesion onset. Patients for whom no lesion appeared will be censored at the date of extubation or at the date of discharge from intensive care or at D28. Patients who died will be censored at their date of death.

The grade of skin lesions (NPUAP scale) and mucosal lesions (Rompis scale) will be collected for each lesion. If the patient has no lesions, a grade=0 on the corresponding scale will be retained. If a patient presents several lesions, the maximum grade observed will be retained.

An ordinal logistic regression model controlling for intubation time and study design will be applied to compare both types of fixation.

The incidence of peri-oral lesions (expressed per 1000 ventilator days) will be calculated and described in each group: number of patients with at least one lesion / total number of ventilator days (up to 1ère lesions in patients with one lesion)

The maximum number of injuries per day will be estimated and compared using a linear model taking into account the study design.

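### The primary logistic model adjusts for how long the tube stayed in, which the fixation can change, so its odds ratio is not the total effect of the strategy on lesion risk before day 10

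*Protocol*

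**What the plan says.** The main objective (Protocol 2.1.1) is to show that the tape strategy lowers the risk of a peri-oral lesion before the tenth day. The endpoint (2.1.2) is binary: "Appearance of at least one peri-oral lesion during the first ten days of maintaining the orally inserted endotracheal tube".

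Section 6.2.1 fixes the design terms for all criteria: "The type of fixation, the period and the center (=cluster) will be taken into account in the model as fixed effects", with the centre-by-period interaction as a random effect. For the primary criterion it plans a description by arm, "The percentage of patients with at least one peri-oral lesion will be estimated with a 95% confidence interval for both types of fixation", and then the model: "A logistic regression model taking into account the duration of the patient's endotracheal tube retention and the study design will be applied". For lesion grade, under Secondary criteria: "An ordinal logistic regression model controlling for intubation time and study design will be applied to compare both types of fixation".

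Three other places link tube retention to the device:

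- Section 2.2.1 has as a secondary objective: "Verify the effectiveness of the device in maintaining the endotracheal tube in terms of self-extubation from intubation until extubation or D28".
- Section 5.2.2 lists, among expected events of putting the device into use, "Unscheduled extubations: self-extubations and accidental extubations during care", at 7 to 16% of patients according to its reference 17.
- Section 5.2.3 names self-extubations among the events of interest that it describes as brought about by the two devices.

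**The concern.** A covariate in the primary model of a randomised comparison should be fixed before the intervention can act on it. Tube-retention time is not. It ends at planned extubation, unscheduled extubation, death or discharge, and the trial sets out to learn whether the two fixations differ on one of these.

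Two things follow if they do differ. First, a fixation that holds the tube longer exposes the patient longer, and any lesions this causes belong to the effect of the strategy; adjusting for duration removes them. Second, sicker patients plausibly stay intubated longer and also get more lesions. Duration would then be a common consequence of device and severity, and conditioning on it relates the two within strata of duration, which the design otherwise prevents.

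At stake is the meaning of the headline result. The duration-adjusted odds ratio compares patients with the same observed retention. The objective asks what happens to lesion risk when a unit adopts one strategy or the other.

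**Working it through.** **1. How duration enters.** The Poisson models in the same section use the word offset, and the ordinal model is said to control for intubation time. The natural reading of the primary sentence is therefore covariate adjustment. Functional form and any cap at day 10 are not stated, so several forms were tried.

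**2. The plan's own figure: does 768 depend on duration?** Inputs from 6.2.2: 35% against 20%, power 90%, alpha 5% (taken as two-sided), intra-class correlation 0.10, inter-class correlation 0.05, 16 centres.

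- Per arm, individually randomised, unpooled variance: (1.960 + 1.282)² × (0.35×0.65 + 0.20×0.80) / 0.15² = 180.96.
- Design effect at 24 per centre-period: 1 + 23×0.10 − 24×0.05 = 2.1.
- Total at that size: 180.96 × 2.1 × 2 = 760.
- Solving for the centre-period size m: m = 0.9×180.96 / (16 − 0.05×180.96) = 23.4, rounded up to 24, so 16 × 2 × 24 = 768.
- Power at 768 is 90.3% (unpooled) or 89.8% (pooled).

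The figure reproduces and contains no duration term.

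**3. How far adjustment moves the odds ratio.** The documents give no retention distribution and no difference between devices, so everything here is assumed. In model 1 (600,000 patients per scenario), retention has a log-normal form with median about 7 days, self-extubation falls at a uniform time, and the daily lesion hazard is constant and set to give 35% and 20% when both arms have 11.5% self-extubation. A frailty version adds one factor that lengthens retention and raises lesion hazard. Adjusted ranges cover linear duration, log duration and duration capped at day 10. Odds ratios are tape against cord.

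| Daily lesion hazard | Self-extubation, cord / tape | No frailty: unadjusted | No frailty: adjusted | Frailty: unadjusted | Frailty: adjusted |
|---|---|---|---|---|---|
| Lower with tape | 11.5% / 11.5% | 0.469 | 0.453–0.460 | 0.468 | 0.427–0.440 |
| Lower with tape | 16% / 7% | 0.497 | 0.457–0.475 | 0.492 | 0.423–0.448 |
| Lower with tape | 7% / 16% | 0.442 | 0.444–0.450 | 0.445 | 0.431–0.432 |
| Equal | 11.5% / 11.5% | 1.007 | 1.006–1.007 | 1.006 | 1.003–1.004 |
| Equal | 16% / 7% | 1.071 | 1.014–1.043 | 1.062 | 0.990–1.023 |
| Equal | 7% / 16% | 0.946 | 0.971–0.998 | 0.954 | 0.986–1.018 |

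Model 2 uses exponential retention with a planned mean of about 9 days, frailty terms of −0.4 and +0.5 on the log-hazards of planned extubation and lesion, and duration capped at day 28 or day 10:

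- Tape halves the lesion hazard, cord 16% / tape 7%: 0.53 becomes about 0.43, a shift of ln(0.53/0.43) = 0.21.
- Tape halves the lesion hazard, equal retention: 0.50 becomes 0.44 to 0.45, a shift of 0.11 to 0.13.
- Equal hazard, cord 16% / tape 7%: 1.07 becomes 0.98 to 0.99.
- Equal hazard, cord 7% / tape 16%: 0.94 becomes 1.02 to 1.03.

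**4. Reading the shifts.** The largest is about 0.2 on the log scale. In the same model, 0.11 to 0.13 appears even when retention is equal. That part is non-collapsibility of the odds ratio, not confounding; the remaining 0.08 to 0.10 comes from the difference in retention.

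**5. Scale.** The standard error of the log odds ratio at 35% against 20% with 384 per arm is √{2.1 × [1/(384×0.2275) + 1/(384×0.16)]} = 0.24. The largest shift is a little under one standard error, and most are well below half of one.

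**6. A wider contrast.** At an assumed 5% cord / 30% tape with equal lesion hazard, model 1 without frailty goes from 0.847 to between 0.916 and 0.989; with frailty, from 0.864 to between 0.956 and 1.043.

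**The case against.** The best defence is that exposure time matters. The introduction speaks of lesions arising while the tube is in place, and an unadjusted comparison would credit a fixation with fewer lesions merely because it loses the tube sooner. That aim is reasonable, but a covariate that the device may affect is a poor way to meet it. The protocol already plans two analyses of exposure: time to first lesion, and patients with a lesion per 1000 ventilator days.

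Lesion percentages by arm with confidence intervals are also planned, so the raw risks will be visible. That helps, but the logistic model is the only between-arm comparison described for the primary endpoint. A cap at day 10 may be written elsewhere; it would limit the use of time after the endpoint is settled, but would not make duration a baseline variable. Re-intubations are recorded and nurse follow-up runs to the final extubation, so some self-extubated patients resume exposure and the pathway is weaker than in the simulations.

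Several stronger readings are tempting and are not supported:

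- A reader might take 7% and 16% as the rates for the two devices. Section 5.2.2 gives one range for unscheduled extubations of all kinds, including accidental ones during care.
- A reader might infer that adjustment can reverse the trial's conclusion. In the simulations the sign changes only near the null; with a halved lesion hazard and 7% against 16% in either direction, every odds ratio stays between 0.42 and 0.53.
- A reader might call the equal-retention shift bias, or say that duration alone makes the odds ratio conditional. That shift is largely non-collapsibility, and the centre terms already make the odds ratio conditional.

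**Conclusion.** The point holds. The primary model conditions on a variable observed after allocation which the protocol's own objectives and safety sections treat as open to influence by the fixation. Its odds ratio is not the total effect of the strategy on lesion risk before day 10. The ordinal grade model shares the defect.

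The documents fix neither the size nor the direction of the distortion. Under an assumed 7% against 16% contrast and the two retention models above, the shift is at most roughly 0.2 on the log odds scale, part of it non-collapsibility. This is a modest distortion in the primary analysis, not evidence that the trial would reach the wrong conclusion. It also gives no ground for questioning the sample size, since 768 reproduces without any duration term.

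**What to change.** In 6.2.1, Main criterion, fit the logistic model with fixation, period and centre as fixed effects and centre-by-period as a random effect, as that section already sets out, plus covariates measured at day 0 at most. Remove intubation time from the ordinal model for NPUAP and ROMPIS grade in the same way. Report the duration-adjusted models as labelled sensitivity analyses, stating how duration is defined and capped. Leave exposure time to the planned time-to-first-lesion and per-1000-ventilator-day analyses.

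The change takes a sentence for each model. The sample size stays at 768 with power of about 90%. The cost is a small loss of the precision that duration would have explained.
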